## Discussion

This paper describes the HEI trial which will examine intervention programs to reduce harm from MSDs and associated stress seen in women as a result of housework. This will be the first comprehensive study to examine the impact of a participatory health promotion program based on a participatory ergonomic approach to reducing musculoskeletal disorders and improving the quality of life in housewives. The ultimate goal of the study is to improve the quality of life, increase work ability, and reduce stress and the severity of musculoskeletal pain in housewives. Housewives in Iran account for a high percentage of the population. Despite the high prevalence of skeletal disorders affecting this community, no interventions have been made to reduce their musculoskeletal injuries, despite the potential benefits to individuals, families, and society. Therefore, this study aims to identify factors underlying musculoskeletal disorders and implement a purposeful intervention program as an effective step to reduce these disorders and improve the quality of life of housewives in Iran.

This study has several robust design features detailed as follows:
*The use of a mixed-methods protocol to identify risk factors:* Housework refers to a series of routine activities done by a person during the day. Thus, housewives are exposed to multiple psychosocial and biomechanical risk factors. To the best of our knowledge, to date no study has been conducted to identify the multiple psychosocial and biomechanical risk factors that account for musculoskeletal disorders among housewives to design an educational intervention program for the target population. As such, psychosocial stressors will be identified in this study using in-depth and face-to-face interviews. Besides, using the JSA method, the living and work environments of housewives will be assessed, and the most important biomechanical risk factors will be identified. Accordingly, a training intervention program that is bespoke to the population of housewives under study will be implemented.*The use of a multidisciplinary (biomechanical and psychosocial) method to implement health promotion training programs:* Based on the reviews that have been done by the research team, the few studies that have been conducted to reduce musculoskeletal disorders in housewives have focused on only one of the known risk factors. However, we know there is a multiplicity of risk factors, so there is now a need to conduct a study using comprehensive interventions in this target group. Numerous studies have shown the interactive effects of biomechanical risk factors such as poor physical conditions and workload, and psychosocial risk factors such as lack of support from others have concluded that the interactive effect of risk factors underlying musculoskeletal disorders is broader than the effect of each risk factor alone. Thus, the present study will examine the gap in the literature to find out whether multidisciplinary interventions are more effective in reducing musculoskeletal disorders among housewives than biomechanical or psychosocial interventions performed separately. Accordingly, four separate groups will be evaluated in this study. This being so, we will be able to deduce which of these interventions is most effective in reducing musculoskeletal disorders.*Performing a randomized controlled trial:* This study will be the first randomized controlled trial performed on housewives to evaluate the effectiveness of comprehensive and multifaceted interventions. Randomized controlled trial designs are held as the gold standard, with best internal validity and least distortion in clinical interventions and healthcare. However, they have rarely been used to evaluate the effectiveness of intervention programs in informal work environments such as the home and housewives’ communities. The evaluations of this study will show that these interventions are possible and feasible in work environments, including the home environment.*The use of participatory ergonomics to implement the intervention program:* Using participatory ergonomics is another high-quality contribution of this study, as this technique engages end-users in the entire study process. According to the principles of this ergonomic approach, improving the health literacy level of housewives will increase their motivation and participation in intervention programs and afford more effective implementation. In addition, the use of network communications and facilitator training in the present study can significantly affect the effectiveness of interventions [30, 31].*Follow-up period:* The gap in the majority of intervention studies is that they have focused on short-term results. The present study explores the effectiveness of the training intervention over a longer period: collecting data at three time points: before the intervention (baseline) and follow-up 3 and 6 months after the intervention.

We do recognize that this study will have some limitations in so far as we must limit the randomized controlled trial to housewives residing in one region of Iran. This, however, will enable us to maintain good control of the test procedure. Another limitation of this study is the need to use self-reporting tools, and thus, there is the possibility of memory error, lack of clarity, social concerns, and individual biases affecting the results. Nevertheless, to compensate for this necessity, valid standard tools will be used. Besides, it is anticipated that the level of participation in the study will remain high and atrophy in the sample size low, because the intervention will continuously offer a reward to the participants in improvement in WMSDs and quality of life. We anticipate this will be so for all the training groups, even if the time commitment for training differs according to group.

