### The intervention programs

The conceptual framework of the health promotion model will be developed based on phase 1 findings from the qualitative study. Recruitment of women who meet the inclusion criteria will continue until the required sample size is achieved. At this point, all participants will be coded and blindly allocated into one of four intervention groups by the researchers using a permuted block randomization program: (1) biomechanical, (2) psychosocial, (3) multidisciplinary (biomechanical and psychosocial), or (4) control. Based on the design of the randomized controlled trial intervention, the impact of the different intervention programs on musculoskeletal disorders, work ability, and quality of life of the housewives will be evaluated. As shown in Fig. 1, measures will be collected at baseline, after 3 months, and after 6 months of following their respective program.

To implement the content of the three intervention programs, a participatory ergonomic approach will be used. The effectiveness of this approach in ergonomic interventions depends on the ability and active cooperation of participants [29]. The required training content for participants in the psychosocial intervention will be provided following the conceptual framework developed in the qualitative study and the resulting theory. Similarly, for participants in the biomechanical intervention group, the required training will be provided following the conceptual framework derived from the qualitative study and job safety analysis (JSA) method. Finally, the multidisciplinary intervention group will receive the training provided to the psychosocial and biomechanical groups: that is, they will do both interventions. The multidisciplinary groups will receive both of the other two interventions in full.

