### Sample size and power calculations

Following the study conducted by Shariat [37], which similarly used a three-arm, parallel, RCT to investigate MSDs in office workers, the sample size we require in the quantitative phase to provide ample power was calculated as 30 persons for each group. This sample size was calculated to be sufficient at an alpha of 0.05 and a power of .80, to test for a difference between the groups. Nevertheless, sample size calculations are sensitive to error and complicated when drawing upon incomplete information in the literature [38]. Additionally, experience indicated we must consider a potential dropout rate of 30%. Hence, according to the following formula, we should work with an initial recruitment target of 40 participants in each group:
$$ n=\frac{{\left({Z}_{1-\frac{\alpha }{2}}+{Z}_{1-\beta}\right)}^2\left({\delta_1}^2+{\delta_2}^2\right)}{{\left(\overline{{\overline{X}}_1}-{\overline{X}}_2\right)}^2}=\frac{{\left(1.96+0.84\right)}^2\left({20.2}^2+{21.1}^2\right)}{{\left(-15\right)}^2}=29.9\cong 30 $$

N=30+30(0.3)≅40

In line with this approach, a total of 160 housewives aged 20–65 years with WMSDs will be recruited based on the health records available in the health centers of Akbarabad-Kavar city by taking into account the inclusion and exclusion criteria given in Table 1. Participants will be allocated into four groups (the three intervention groups plus one control group) based on permuted block randomization. The allocation is concealed by using opaque, sealed envelopes that are consecutively numbered and included each group’s name. Sampling using this randomization process gives each participant an equal chance of being placed in each group [39].

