### Data analysis

#### Phase 1

To perform the process of qualitative content analysis, the audio file of each interview will be listened to attentively several times on the same day and it will be transcribed verbatim. To keep the data from the interviews confidential, a code will be assigned to each transcript. To come up with a general impression of the interviews and become fully immersed in the data, the audio files of the interviews and the transcripts will be reviewed several times, and any possible ambiguities and inconsistencies will be removed by comparing the audio files and the transcripts. The interviews will be audiotaped and a summary of the key issues in each interview will be then sent to each participant to ensure that the researcher will have accurately interpreted that participant’s comments (a “member check”) [26]. The process of data analysis will be performed continuously and simultaneously with the data collection process. All words, sentences, and paragraphs that are related in the analysis process will be considered as a single semantic unit. After merging the semantic units, the codes will be extracted. The codes together form the subcategories and then the main categories. Finally, upon the abstraction of the categories, the relevant themes will be identified. MAX.QDA software will be used to manage the data [40].

#### Phase 2

The collected data will be analyzed with SPSS software using descriptive statistics (including frequency, frequency percentage, mean, and standard deviation) and inferential statistics. We will undertake both “intention to treat” and “per protocol” approaches to the inferential statistical analyses to achieve fully understand the outcomes and manage bias in the face of any drop out. To compare the differences between the values obtained before the intervention and 3 and 6 months after the intervention in each group, generalized mixed models of analysis of variance for repeated measures will be used. We will also calculate differences between means of the independent groups with their respective 95% confidence intervals. All tests will be performed at a significance level of 0.05 (p <0.05). The Kolmogorov-Smirnov test will be used to test the normality of the data. The per protocol analyses will only include the participants who complete the intervention to which they were allocated.

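### Between-arm results are described as differences of group means rather than as contrasts from the planned mixed model, so the intention-to-treat comparison is exposed to outcome-related dropout, in a direction the protocol does not fix

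*Protocol article*

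**What the plan says.** All references are to the protocol article.

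- **Sample size and power calculations:** "experience indicated we must consider a potential dropout rate of 30" per cent. The target is raised from 30 to 40 women per group, 160 in all.
- **Discussion, limitations:** attrition is expected to be low because "the intervention will continuously offer a reward to the participants in improvement in WMSDs and quality of life". The next sentence adds "We anticipate this will be so for all the training groups". Control is not mentioned there.
- **The intervention programs:** "measures will be collected at baseline, after 3 months, and after 6 months of following their respective program". Control is offered a programme only after the final evaluation.
- **Secondary outcomes:** the quantitative question is which of the three interventions works best on quality of life, work ability, symptoms and stress. That is a between-arm question.
- **Data analysis, Phase 2:** intention-to-treat and per-protocol analyses are both planned and are presented as the way to handle bias from dropout. Repeated-measures mixed models are named for comparing values before and after the intervention within each group. For the comparison of arms the text says: "We will also calculate differences between means of the independent groups with their respective 95% confidence intervals". The per-protocol set contains only women who complete their allocated programme.

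**The concern.** The analysis section gives the two tasks to two different tools. The mixed model, which can use a woman's earlier visits after she has left, is assigned to change over time within a group. The comparison of arms is given as a difference of means. A woman who leaves before a visit has no value to contribute to a simple mean at that visit. If the means are of that kind, the intention-to-treat label does not bring her back in, and the per-protocol analysis selects further.

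This matters because the Discussion itself gives a reason for staying that is an outcome: women stay because their disorder and quality of life improve. If improvement keeps women in, lack of improvement may let them go. Should that selection be stronger in a training arm than in control, the training arm's observed mean would look better than the mean of the women randomised to it, and an ineffective programme could appear to work. Should selective loss be heavier in control, a useful programme could look weaker than it is.

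**Working it through.** **Inputs from the plan.** SDs 20.2 and 21.1, difference 15, z-values 1.96 and 0.84, dropout 30%, 40 per group. The outcome and scale behind the SDs and the difference are not named.

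**The plan's own figure.** n = (1.96 + 0.84)² × (20.2² + 21.1²) / 15² = 7.84 × 853.25 / 225 = 29.7. The article prints 29.9; both round to 30. Then 30 + 30 × 0.3 = 39, taken to 40. With 30% lost, 40 × 0.7 = 28 women remain per arm.

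**Step 1: one-sided selection, by formula.** Assumption: 30% leave each arm; in the training arm leaving is related to outcome with correlation ρ, in control it is not. The ρ values are assumed; the article gives none.

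- Common SD = √((20.2² + 21.1²)/2) = 20.65.
- Shift = ρ × φ(z₀.₃₀)/0.70 × SD = ρ × 0.497 × 20.65.
- SE of the difference = 20.65 × √(2/28) = 5.52.
- Two-sided false-positive rate = P(|Z + shift/SE| > 1.96).

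| ρ (assumed) | Shift, points | Share of 15 | False-positive rate |
|---|---|---|---|
| 0.2 | 2.1 | 14% | 6.6% |
| 0.3 | 3.1 | 21% | 8.6% |
| 0.5 | 5.1 | 34% | 15.3% |

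**Step 2: does the direction hold under other assumptions?** This is a large simulation (400,000 per arm) with SD 20.65, higher score better, true effect 0 and logistic dropout. The slope is the rise in log-odds of leaving per SD of worse outcome. Rates by arm and slopes are assumed. A positive bias favours the programme.

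| Training: dropout, slope | Control: dropout, slope | Bias in difference of observed means |
|---|---|---|
| 30%, 0.5 | 30%, 0 | +2.9 |
| 30%, 1 | 30%, 0 | +5.3 |
| 30%, 2 | 30%, 0 | +7.9 |
| 10%, 1 | 10%, 0 | about +2 |
| 30%, 1 | 30%, 1 | about 0 |
| 10%, 1 | 30%, 1 | −3.3 |
| 30%, 0 | 30%, 1 | −5.2 |

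With a true effect of 15 the biases are nearly the same. The sign depends on which arm loses women more selectively.

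**Step 3: would the planned model help?** Here dropout was made to depend on the observed 3-month value, with an assumed correlation of 0.6 between months 3 and 6. The difference of observed 6-month means was compared with a likelihood-type estimate that uses the 3-month values.

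| Training: dropout, slope | Control: dropout, slope | Observed means | Using 3-month values |
|---|---|---|---|
| 30%, 1 | 30%, 0 | +3.2 | 0.0 |
| 30%, 1 | 30%, 1 | 0.0 | 0.0 |
| 10%, 1 | 30%, 1 | −2.0 | 0.0 |
| 30%, 0 | 30%, 1 | −3.1 | +0.1 |

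The near-zero bias follows from dropout having been set to depend on an observed value. It shows what the model can do in that case, not that this trial is in that case.

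**The case against.** Five points can be made for the plan.

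1. **The group means may be model-based.** The article does not say they are raw means of completers, and the wording on change within each group could be read loosely as comparing change across groups. This stands as an ambiguity, and it is why the point is conditional. It does not remove it: as written, the model is attached to within-group change and the arm comparison is a separate, additional calculation.
2. **Missing-data rules belong elsewhere.** A reader might infer that the fault is the absence of a rule for scoring dropouts. That alone is no finding, because an article commonly leaves it to the full protocol or analysis plan. The point here is the allocation of methods that the article does state.
3. **The Discussion can be over-read.** It speaks first of participation in the study generally, and the sentence on training groups concerns their differing time commitment. It does not say that women who fail to improve will leave, or that control dropout is unrelated to outcome. This stands. The reasoning makes outcome-related dropout plausible; it does not describe its pattern by arm.
4. **Thirty per cent against low attrition.** A reader might infer a contradiction. The first is a planning allowance and the second an expectation, so this is a tension only.
5. **The sizes rest on the 30%.** If dropout were 10% (an illustrative figure, 36 left per arm), the formula at ρ = 0.3 gives 0.3 × 0.195 × 20.65 = 1.2 points and a false-positive rate of about 5.7%. This stands: the effect shrinks with the dropout rate.

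**Conclusion.** The concern holds as a risk. The trial's quantitative question is a comparison of arms. The article describes that comparison as a difference of group means, and keeps for within-group change the model that could make better use of incomplete data. If the means are of women still observed, the intention-to-treat contrast is open to bias from dropout related to outcome, and the article's own account of retention makes such dropout plausible.

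A reader might go further and infer that the comparison is biased towards the programmes. The article does not support that: it gives no dropout rates by arm and no account of why control women would leave. Bias favours the programmes only if women who do not improve leave the training arms more selectively than control. Equal mechanisms give about zero. Lower dropout in training than in control, which would fit the Discussion's optimism, gave −3.3 points in the simulation.

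The shift of about 2 to 5 points and the false-positive rates of 6.6% to 15.3% are illustrations, not properties of this plan. They require 30% loss, selection in one arm only, assumed correlations of 0.2 to 0.5, and an SD taken from an unnamed outcome.

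**What to change.** In Data analysis, Phase 2:

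- State that the intention-to-treat between-arm differences at 3 and 6 months, with 95% confidence intervals, come from arm-by-visit terms of the repeated-measures mixed model already planned, fitted to all observed visits of all randomised women. This is valid if dropout depends on observed values.
- Add one sensitivity analysis that allows dropout to depend on unobserved values, for example imputing missing training-arm outcomes from the control arm's course.
- Report dropout by arm, so that readers can judge which way any selection may run.

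The cost is a few sentences and a little extra analysis. Sample size, visits and instruments are unchanged. The estimates may turn out less favourable to the programmes.

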## Conclusion

This study will provide a practical approach to improving quality of life, reducing stress, reducing musculoskeletal disorders, and improving work ability among housewives. If the interventions are effective, the training protocol that will be developed in the present study will have great potentials for being implemented as an educational intervention among housewives and in other environments.

### Trial status

The study is ongoing. Recruitment opened in November 2020 and will continue until all housewives required for the trial are enrolled, planned to be in April 2021. The duration of the study period will be 1.5 years and will be finished in April 2022.

## Data Availability

Not applicable. The manuscript does not report data. The datasets subsequently generated and/or analyzed during the current study may be made publicly available following conclusion of ongoing research. Requests for data may be made at any time to the corresponding author.

## Abbreviations

WMSDs: Work-related musculoskeletal disorders
MSD: Musculoskeletal disorder
CONSORT: Consolidated Standards of Reporting Trials
MMR: Mixed methods research
RCT: Randomized controlled trial
VAS: Visual analog scale
REBA: Rapid Entire Body Assessment
WAS: Work Ability Score
HADS: Hospital Anxiety and Depression Scale
SF-36: Short Form Health Survey 36 Items Version 1.0
